9.1.3. At follow-up

1) Testing dates

The observations and tests listed below will be performed every 3-6 months, counting from the first day of the protocol treatment. Follow-up will be performed for 3 years after the enrollment of the last subject. Entries in case report forms will be made once annually until Year 3, after which all tests and observations will be performed 3 years after the enrollment of the last subject.

2) Observations and tests

Outcome

Confirmation of outcome: Survival (date of last confirmation of survival)

Death (Cause of death: primary disease, other cancer, other, date of death)

Lost to follow-up (date of last confirmation of survival)

Method of confirmation: clinic appointment, other

*When survival status cannot be confirmed directly because the subject transferred to another hospital or the like, every effort will be made to obtain outcome information from the subject’s new hospital.

Confirmation of relapse and secondary cancer

Presence of relapse (If present, the following items will be entered in the outcome report.)

Relapse site: local, distant (brain, bone, lung, liver, lymph node, adrenal gland, skin, other)

Confirmation method and date confirmation performed: simple chest radiography, ultrasonography, CT, MRI, PET, histopathology, cytology, other

Confirmation date (If diagnosed by multiple diagnostic methods, the date the earliest test was performed.)

Presence of secondary cancer (If present, the following items will be entered in the outcome report.)

Site of occurrence of secondary cancer (head and neck, lung, esophagus, stomach, other)

Diagnostic method and date diagnosis performed: simple chest radiography, ultrasonography, CT, MRI, PET, histopathology, cytology, other

Date of diagnosis (If diagnosed by multiple diagnostic methods, the date the earliest test was performed.)

*Presence of relapse and secondary cancer will be confirmed in accordance with “Definition of relapse and secondary cancer” in 11.1.

Therapy following protocol treatment: Presence of therapy following protocol treatment

9.1.4. At occurrence of serious adverse events

The reporting technique in “8. Adverse Event Evaluation and Reporting” will be used.

9.2. Observation, test, and reporting schedule

∙Observations and tests (there will be a testing window of ± 14 days starting at Treatment Week 4 and ± 28 days during follow-up.)

| Time performed  Test | Enrollment | Treatment period | | | | | | | Discontinuation | Treatment completion | Follow-up † | Completion of follow-up |
| --- | --- | --- | --- | --- | --- | --- | --- | --- | --- | --- | --- | --- |
|  |  | TS-1-treated arm | | | UFT-treated arm | | | |  |  |  |  |
|  |  | 1st cycle | | Beginning of each subsequent cycle | Day 1 | Day 8 | Day  29 | Every 4 weeks thereafter |  | 1 year after starting protocol treatment | Every 3-6 months | 3 years after enrollment of last subject |
|  |  | Day 1 | Day 8 |  |  |  |  |  |  |  |  |  |
| Basic information / background | ● |  |  |  |  |  |  |  |  |  |  |  |
| PS | ● | ● | ● | ● | ● | ● | ● | ● | ● | ● |  |  |
| Compliance |  | ● | ● | ● | ● | ● | ● | ● | ● | ● |  |  |
| Clinical laboratory tests | ● | ● | ● | ●* | ● | ● | ● | ● | ● | ● |  |  |
| Signs and symptoms, adverse events | ● | ● | ● | ● | ● | ● | ● | ● | ● | ● |  |  |
| Tumor markers | ○ | ○ | ○ | ○ | ○ | ○ | ○ | ○ | ○ | ○ | ○ | ○ |
| Imaging or pathological tests | ○* (Every 3-6 months) | | | | | | | | | | | |
| Confirmation of relapse and secondary cancer | Confirmed as appropriate based on clinical symptoms, etc. | | | | | | | | | | | |
| Presence of therapy following protocol treatment |  |  |  |  |  |  |  |  |  | ● | ● | ● |
| Confirmation of outcome |  |  |  |  |  |  |  |  | ● | ● | ● | ● |

●: Must be done. ○: To be done when possible

●*: To ensure patient safety, it is desirable to perform clinical laboratory tests at times besides the beginning of each cycle.

○*: Diagnostic imaging or pathological tests will be performed every 3-6 months to confirm the presence of relapse or secondary cancer. However, appropriate tests will also be performed whenever relapse or secondary cancer is suspected.

†: Will be performed every 3-6 months, counting from the protocol treatment initiation day.

⋅ Reporting When reporting to the Data Center, data will be input according to the following schedule.

| Reporting time  Input sheet | Enrollment | Immediately after treatment initiation | Treatment period | | | | | | Follow-up |
| --- | --- | --- | --- | --- | --- | --- | --- | --- | --- |
|  |  |  | TS-1-treated arm | | | UFT-treated arm | | |  |
|  |  |  | 4th cycle  (12 weeks) | 8th cycle  (24 weeks) | Completion of protocol treatment  (1 year) | 3 months | 6 months | Completion of protocol treatment  (1 year) | Discontinuation / completion to 3 years after the enrollment of the last subject  (2 years, 3 years, and 3 years after the enrollment of the last subject) |
| Subject enrollment form | ● |  |  |  |  |  |  |  |  |
| Baseline report |  | ● |  |  |  |  |  |  |  |
| Treatment report |  |  | ● | ● | ● | ● | ● | ● |  |
| Outcome report |  |  |  |  | ● |  |  | ● | ● |

*All observations and tests are scheduled to be performed at one time 5 years after enrollment of the last subject.

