7.1.2. Experimental treatment arm (TS-1-treated arm)

1) Treatment regimen

TS-1 will be administered by the oral route daily for 14 days (Day 1-14) with a 7 day rest period (Day 15-21). The daily dose (80 mg, 100 mg, or 120 mg), which is based on body surface, will be divided into 2 doses daily (after breakfast and dinner) This 21-day (3-week) period will comprise 1 cycle and will be repeated for 1 year from the protocol treatment initiation day (about 18 cycles will be administered). New cycles will not be started after 1 year has elapsed from the protocol treatment initiation date. After completion of UFT treatment, subjects will be followed for up to 5 years (for 3 years after enrollment of the last subject), and antineoplastic therapy will not be performed until metastases or relapse are confirmed.

Daily oral TS-1 treatment for 14 days

7-day rest period

Day 1 Day 14 Day 21

TS-1 dose and administration method

| Body surface area | Single dose at treatment  initiation (FT equivalent) | Daily dose  (FT equivalent) | Breakfast | Lunch | Dinner |
| --- | --- | --- | --- | --- | --- |
| < 1.25 m^2^ | 40 mg/dose | 80 mg | 40 mg | - | 40 mg |
| ≥ 1.25 m^2^ to <1.5 m^2^ | 50 mg/dose | 100 mg | 50 mg | - | 50 mg |
| ≥ 1.5 m^2^ | 60 mg/dose | 120 mg | 60 mg | - | 60 mg |

2) TS-1 specifications

TS-1 Capsules 20: 20 mg FT equivalent per capsule

TS-1 Capsules 25: 25 mg FT equivalent per capsule

7.2. Criteria for changing dose and schedule (Rest days or reduced dose days will be recorded in the chart without fail.)

The following terminology will be used for change criteria.

Rest: A temporary holiday during which drug is not administered during the protocol treatment dosing period after which treatment can be resumed if the conditions are satisfied.

Dose reduction: Administration of less than the specified dose

Discontinuation: The protocol treatment is discontinued, and treatment will not be resumed during the subject’s participation in the study.

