7.2.1. Rest criteria and resumption criteria

When starting a TS-1 cycle (after the rest period from the previous cycle) and when performing tests during UFT treatment, it will be confirmed that all test values satisfy the dosing criteria before resuming treatment. When the dosing criteria are not satisfied, treatment will be withdrawn and resumed according to the following criteria.

1) Rest criteria

If the following adverse events which apply to the rest criteria occur during the drug treatment period, drug treatment will be immediately withdrawn, the (sub)investigator will wait until the values return to at least the treatment resumption criteria before resuming treatment.

The (sub)investigator will decide whether or not to withdraw treatment when rest criteria apply to the laboratory values of subjects whose baseline values are close to the rest criteria.

Rest criteria *Non-hematologic toxicities: Adverse events from sections of the CTCAE other than Blood/Bone Marrow

| Parameter | | Criterion for prescribing rest |
| --- | --- | --- |
| Hematologic toxicities | WBC | < 3,000 /mm^3^ |
|  | Neut | < 1,500 /mm^3^ |
|  | PLT | < 75,000 /mm^3^ |
|  | Hb | < 9.0 g/dL |
| Non-hematologic toxicities  * | T.Bil | ≥ 2.0 mg/dL |
|  | AST⋅ALT | ≥ 100 IU/L |
|  | Cr | ≥ 1.2 mg/dL |
|  | Other adverse events | ≥ Grade 2 |
| Other instances in which the investigator determines that rest is necessary because of adverse events, etc., in order to continue the protocol treatment. | | |

2) Treatment resumption criteria

(1) UFT-treated arm

After withdrawing treatment, the investigator will wait until the treatment resumption parameters return to normal to resume treatment. The dose at treatment resumption will be determined in accordance with the dose reduction criteria (refer to 7.2.2.). When the rest period exceeds 28 days due to adverse events, the subject’s protocol treatment will be discontinued.

(2) TS-1-treated arm

After a rest of at least 1 week in the TS-1-treated arm, it will be confirmed that the following treatment resumption criteria have been satisfied before resuming TS-1 treatment. The dose at treatment resumption will be determined in accordance with the dose reduction criteria (refer to 7.2.2.). When the rest period exceeds 28 days due to adverse events, the subject’s protocol treatment will be discontinued.

Example) When rest starts on Day 8 of the first cycle

after at least 1 week of rest, it is confirmed if treatment can be resumed.

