9.1.2. During the study period

1) Testing dates

(1)TS-1-treated arm (experimental treatment arm)

The observations and tests listed below will be performed on the first dosing day (Day 1) and Day 8 of the first cycle and on the first day of the second and all subsequent cycles. The results will be entered in the case report forms via the web at the fourth and eighth cycles and at completion of treatment after 1 year.

(2)UFT-treated arm (control treatment arm)

The observations and tests listed below will be performed on the first dosing day (Day 1), Day 8, and Day 29 during the first 4 weeks and then every 4 weeks, starting at Week 5. The results will be entered in the case report forms via the web at 3, 6, and 12 months (completion of treatment).

2) Observations and tests: The following tests will be performed on the prescribed testing days.

Note that only the underlined data below will be reported via the web.

ECOG performance status scale: PS

Test parameters related to the study drugs

Compliance*: Compliance will be confirmed based on the medication record and scored on the following scale. The investigator will score compliance on the following 4-grade scale every 4 cycles for TS-1 and every 3 month for UFT.

*The percentage of drug taken during the dosing period will be calculated. Note that the number of capsules not taken during the rest period will not be included in the calculation.

(1) Took 100% (2) Took ≥ 75% and < 100%, (3) Took ≥ 50% and < 75%, (4) Took < 50%

Rest: presence of rest, reason for rest,

duration of rest (rest initiation date and treatment resumption date)

Dose reduction: presence of dose reduction, reason for dose reduction, daily dose after reduction

Discontinuation: presence of discontinuation, discontinuation date, reason for discontinuation

Submission of follow-up data after withdrawal of consent: possible, not possible

Clinical laboratory tests

Hematology: WBC, Neut, PLT, Hb

Blood biochemistry: T.Bil, AST, ALT, Cr, LDH*, ALP*, CRP*, Na*, K*, Cl*, Ca*

*Will be done when possible

(Only WBC, Neut, PLT, Hb, T.Bil, AST, ALT, and Cr will be entered in the record; the presence of adverse events in each test and the highest grade will be entered.)

Tumor markers: SCC or CYFRA

(Will be measured if necessary. Results will be entered via the web if measured within 30 days before or after discontinuation or completion of protocol treatment.)

Adverse events

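### The blanket ±14-day window in Protocol 9.2 covers the laboratory tests that gate dosing: two on-schedule UFT tests can be 56 days apart, and the age of a TS-1 cycle-start sample is left open

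*Protocol*

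**What the plan says.** Protocol section 9.2 attaches one window to its whole table of observations and tests: "there will be a testing window of ± 14 days starting at Treatment Week 4 and ± 28 days during follow-up". Laboratory tests are mandatory during treatment in both arms, and the window makes no exception for them.

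The nominal dates are in section 9.1.2. TS-1 patients are tested on Day 1 and "Day 8 of the first cycle and on the first day of the second and all subsequent cycles". UFT patients are tested on Day 1, Day 8 and "Day 29 during the first 4 weeks and then every 4 weeks, starting at Week 5".

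Section 7.2.1 says what the tests are for. In the TS-1 arm the check against the dosing criteria is made "When starting a TS-1 cycle (after the rest period from the previous cycle"). In the UFT arm it is made at the test visit itself: "when performing tests during UFT treatment, it will be confirmed that all test values satisfy the dosing criteria before resuming treatment". If a rest criterion is met, "drug treatment will be immediately withdrawn".

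On dosing, section 7.1.2 says "TS-1 will be administered by the oral route daily for 14 days (Day 1-14) with a 7 day rest period (Day 15-21"), and that "about 18 cycles will be administered" over the year. Under section 7.1.1, UFT is taken every day for a year.

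Two other places matter. Section 5.1, item 10, sets a 14-day limit on the age of laboratory values, but only for enrollment. A footnote in 9.2 calls extra laboratory tests desirable, and it is attached only to the TS-1 cycle-start column.

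**The concern.** A window of ±14 days is half of the 28-day UFT interval and two thirds of the 21-day TS-1 cycle. That may suit performance status or compliance scoring. It is wide for blood tests that decide whether a patient goes on taking a cytotoxic drug.

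Of the eight parameters listed in the rest-criteria table of 7.2.1, seven are laboratory values (WBC, neutrophils, platelets, hemoglobin, bilirubin, AST/ALT, creatinine). For those seven, the order to stop at once can work only if blood has been drawn. The UFT arm is the more exposed: it has no cycle start to force a check, so a late test is also a late check. In the TS-1 arm the question is narrower, namely whether an early sample may serve to clear the next cycle.

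**Working it through.** This is calendar arithmetic; the Protocol gives no figure of its own to reproduce. The inputs are the sections set out above. Windows are taken around the nominal dates, and no rest or delay is assumed.

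**Where the window starts.** Day 22 is the first day of Week 4 and Day 29 the first day of Week 5. The window therefore applies from TS-1 cycle 2 and from the UFT Day 29 test onward.

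**UFT**
- Nominal tests fall on Days 29, 57, 85, 113 and so on.
- The Day 57 window is Days 43 to 71; the Day 85 window is Days 71 to 99.
- Largest gap: 99 − 43 = 56 days, which is 28 + 2 × 14. Without a rest, that is 56 days of daily dosing between checks, against 28 planned.
- Recurrence: after a test on Day 99, the Day 113 window closes on Day 127, and 127 − 99 = 28. Two 56-day gaps in a row are impossible. The number of tests and the mean interval of 28 days do not change.

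**TS-1**
- Cycle c starts on Day 1 + 21(c − 1). Cycle 3 starts on Day 43 and cycle 4 on Day 64.
- The early side of the cycle 3 window is Days 29 to 42. Days 29 to 35 are Days 8 to 14 of cycle 2, which are dosing days (7 days). Days 36 to 42 are the rest week (7 days).
- A sample within the window can therefore be 43 − 29 = 14 days old at cycle start, with up to 7 of the previous 14 dosing days still to come when it was drawn.
- Where this can apply: only cycle 1 has its own Day 8 test, so the clear cases are cycles 3 to 18, which is 16 of the 17 starts after cycle 1.
- Largest gap between clearing tests: Day 29 to Day 64 = 35 days (21 planned). Dosing days between them: Days 29 to 35 (7) plus Days 43 to 56 (14) = 21 (14 planned).
- Recurrence: the 35-day gap needs an early test followed by one on the first day of the next cycle. From Day 64, the cycle 5 test falls at most 21 days later (Day 85), or only 7 days later if early (Day 71). The count of 16 starts belongs to the 14-day-old sample, not to the 35-day gap.

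**With narrower rules**
- UFT at ±7 days: 28 + 2 × 7 = 42 days. At ±3 days: 28 + 2 × 3 = 34 days.
- TS-1 sample within 7 days before, or on, the first dosing day: Days 36 to 43 for cycle 3 and Days 57 to 64 for cycle 4. Largest gap 64 − 36 = 28 days, with Days 43 to 56 between, the planned 14 dosing days.

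**The case against.** For TS-1, the more specific text answers most of the point. Section 7.2.1 puts the check after the rest period, 9.1.2 puts the test on the first day of the cycle, and the column in 9.2 is headed accordingly. A post-rest value is almost certainly what was meant. This objection largely stands, which is why TS-1 is the secondary part of the point. What it leaves is that 7.2.1 fixes when values are confirmed and not how old they may be, so the literal early side of 9.2 conflicts with the evident intent. The re-check after at least one week covers rests taken for adverse events, not the routine rest week.

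For UFT, the 56 days are an extreme, with nothing to suggest that they would be typical. Other adverse events of Grade 2 or higher call for a rest without a blood draw, and the investigator may rest a patient at discretion. That is correct. It does not help the patient whose counts or liver or renal values worsen without symptoms, and no section caps the UFT laboratory interval. It is also fair that the Protocol does not show 42 days to be acceptable and 56 not; the exact width is a judgment.

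A reader might infer that the late side of the window lets a TS-1 cycle be given in full before its test (for cycle 3, up to Day 57). The documents do not support this: 7.2.1 requires values to be confirmed before the cycle starts, so a late test is best read as a delayed cycle tested on its actual first day.

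**Conclusion.** The point holds as a cheap improvement of minor patient-safety weight.

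The firm part is UFT: two consecutive on-schedule tests may be 56 days apart instead of 28, and the dosing check moves with them. The weaker part is TS-1: an ambiguity that literally admits a sample up to 14 days old at any of cycles 3 to 18. The 35-day gap with 21 dosing days is possible, but not at consecutive starts.

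These figures rest on windows anchored to nominal dates and on uninterrupted dosing. They are limits of what is allowed, not forecasts. A reader might take them to mean that monitoring is halved throughout, or that the efficacy comparison is at risk. Neither follows: the mean UFT interval stays at 28 days, and nothing here touches disease-free survival, alpha or power.

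**What to change.** Change the wording of section 9.2 as follows:
- Exempt from the ±14-day window the laboratory tests used for dosing decisions under 7.2.1, and keep ±14 days for the other items.
- Give the 4-weekly UFT laboratory tests a narrower window, for example ±7 days. The team may choose another width.
- State that TS-1 cycle-start laboratory tests are taken within 7 days before, or on, the actual first dosing day of the cycle, and before the first dose. Tying the rule to the actual day lets it move with a delayed cycle.

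No extra tests are needed. The cost is slightly less scheduling freedom for sites.

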# Target sample size and study period

10.1. Target sample size

The target sample size is 500 subjects (250 in the TS-1 arm and 250 in the UFT arm).

10.2. Study period

The enrollment and follow-up periods are as follows.

Enrollment period: 3 years (April 2006 to March 2009)

Follow-up period: 3 years after enrollment of the last subject (March 2012)

To study survival, all observations and tests are scheduled to be performed at one time 5 years after enrollment of the last subject (March 2014).

# Definitions of Endpoints

Events defining the endpoints are presented in the following table.

| Endpoint | Event (whichever is earlier) | | |
| --- | --- | --- | --- |
| Overall survival (OS) | Death from any cause | - | - |
| Relapse-free survival (RFS) | Death from any cause | Relapse | - |
| Disease-free survival (DFS) | Death from any cause | Relapse | Secondary cancer |

11.1. Primary endpoint

Disease-free survival (DFS)

The period from the enrollment date to earliest date among the date that relapse was diagnosed, date that secondary cancer was diagnosed, and date of death from any cause. For survivors not diagnosed with relapse or secondary cancer, DFS will be cut off at the last survival confirmation date.

Definition of relapse and secondary cancer

∙Definition of relapse and relapse confirmation date

“Relapse” will be diagnosed when any of the following criteria apply.

(1) Findings on diagnostic imaging (simple chest radiography, ultrasonography, CT, MRI, PET, etc.) that are not secondary cancer will be considered “relapse.” When relapse is diagnosed by multiple diagnostic methods, the date of the earliest test will be considered the “relapse confirmation date.”

(2) When relapse is diagnosed by pathological tests (cytology, biopsy), the date of the earliest test will be considered the “relapse confirmation date.”

(3) An increase in tumor markers will not be considered “relapse.”

∙Definition of secondary cancer (double cancer, multiple cancer) and secondary cancer confirmation date

(1) Definition of secondary cancer

Findings satisfying all of the criteria below from Warren and Gates Diagnostic Criteria 1) will be considered “secondary cancer.”

(1) Each of the tumors exhibits clear malignancy.

(2) Each of the tumors is separate and distinct.

(3) One tumor is not a metastasis of the other.

(2) Definition of secondary cancer confirmation date

(1) When there are findings on diagnostic imaging (simple chest radiography, ultrasonography, CT, MRI, PET, etc.), the date of the imaging will be considered the “confirmation date” and when secondary cancer is diagnosed by multiple diagnostic methods, the date of the earliest test will be considered the “secondary cancer confirmation date.”

(2) When secondary cancer is diagnosed by pathological tests (cytology, biopsy), the date of the earliest test will be considered the “confirmation date.”

11.2. Secondary endpoints

11.2.1. Relapse-free survival (RFS)

The period from the enrollment date to the earlier of the date that relapse was diagnosed or the date of death from any cause. For survivors not diagnosed with relapse, RFS will be cut off at the last survival confirmation date.

11.2.2. Overall survival (OS)

The period from the enrollment date to the date of death for any reason. OS will be cut off at the last survival confirmation date for subjects still alive at that time. For subjects lost to follow-up, OS will be cut off at the last survival confirmation date before they were lost to follow-up.

11.2.3. Adverse events

AEs will be graded according to the JCOG/JSCO Japanese-language version of CTCAE v.3.0.

# Statistical Considerations

12.1. Rationale for target sample size

The results of large-scale comparative studies in Western countries were used as the rationale for the disease-free survival rate in the control arm. This was done because there are no reports of Japanese studies in which UFT treatment was performed on control subjects as in the present study that could be evaluated.

The 3-year disease-free survival rate among subjects that had undergone curative therapy for Stage III, IVA, and IVB squamous cell cancers of the head and neck was approximately 35-45% in subjects that received radiotherapy postoperatively and approximately 40-59% in subjects that received combination radiotherapy and chemotherapy postoperatively.

From these results, it was hypothesized that the 3-year disease-free survival rate would be 50% in the control (UFT) arm. Thus, 216 subjects per arm would be required to have a hazard ratio of 0.7 (3-year disease-free survival rate: 61.6%) for the test (TS-1) arm versus the control arm with an enrollment period of 3 years, follow-up period of 3 years, two-sided α of 0.05, and statistical power of 80%. A sample size of 250 subjects per arm (500 in both arms) was selected because a power of test of at least 80% could be guaranteed with 250 subjects per arm.

